### **Adequacy of protection against risks**

We will be engaging vulnerable individuals in this process, and protocols will be put in place to monitor and respond to participants’ needs at various stages in the study. We anticipate that these measures will be adequate to protecting participants for issues that arise.

- 1) Access to appropriate mental health crisis support will be identified for each university or college recruitment site, and information regarding services will be provided to all participants. Information regarding these crisis support services will be provided to all participants. A prominent crisis-redirect “help” feature is built into the app for students to use to immediately connect them to crisis resource and help lines.
- 2) Key members of the research team will be able to provide emergent clinical input or direction, should the need arise. These members of the research team will also provide direction and training to ensure appropriate, meaningful, and effective engagement with youth, especially vulnerable youth.
- 3) Participants will be provided with information about what kinds of digital user-information will be gathered from the app for the research. This data will only consist of aggregated (group-level) data about usage trends, and therefore the data will be anonymous and will not consist of any information tied to specific individuals.
- 4) A resource pamphlet will be made available to all students in the control group with information about crisis support services and other mental health and wellness resources.

- 5) Being audio-recorded may feel awkward or embarrassing for some participants. It is disclosed to the participants on the consent form for the end-of-study interviews that their interviews will be audio-recorded. If they are uncomfortable, they can choose not to participate in this aspect of the study. If they start to feel uncomfortable during the interview, we will choose to terminate the interview for the well-being of the participant.

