### **Statistical Analysis Plan**

All analyses will be carried out using SAS System 9.4 for Windows. Statistical tests will be 2 sided, with confidence levels of 0.05. Prior to testing, a series of univariate analyses will be carried out to ensure that model assumptions are met. To address the primary study hypothesis, a mixed-effect model will be used to account for the longitudinal nature of the data, and for attrition. Missing values will be treated with maximum likelihood estimation in SAS PROC MIXED, which uses all available information in the data. Intention-to-treat analysis will be used; all participants will be analyzed as they were originally allocated after randomization. As a sensitivity analysis, the final model will be fitted only with subjects for whom there is complete data. Formal help-seeking score will be the dependent variable, with study groups (intervention and control) and time points as predictors, and relevant socio-demographics collected at baseline as covariates to control for possible confounding.

The interaction between study group and time will be included in the model, and linear contrasts will be used to compare the groups, specifically regarding the change from baseline to the final time point. Similar models will be used to address the exploratory hypotheses, which examine different scales and trends, on the effect of the intervention over time. Bonferroni adjustment will be used to control the Type I error rate if multiple comparisons are desired. Generalized estimating equations will be used for the AHSQ, since this scale is binary.

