- An extra sensitivity analysis was conducted where baseline variables significantly associated with dropouts at significance level of 0.20 were added to the primary model. Under the direction of our senior statistician, this is considered a better alternative than the one listed in the protocol which uses completers only. That is because mixed effect models adjusted by maximum likelihood can correct biases caused by missing values as long as the missing values are not associated with information not in the model (Missing At Random – MAR – assumption). By adding baseline variables associated with missing values we increase our chances that we are not violating the MAR assumption. The high level 0.20 was chosen so that we minimize the chances of missing important variables, having in mind that in this case we are more concerned with missing important variables than with including unimportant variables. This was only done for the primary outcome, and reported in our paper. The sensitivity analysis described in the protocol, which keeps only completers, was also conducted and the conclusion was the same.
- Multiple comparisons was not conducted so we did not need to use Bonferroni adjustments. Our secondary analyses are conducted with exploratory nature.

- Since there was no evidence for our primary outcome, we did not conduct the sex- and gender-based analysis.
- We conducted two additional exploratory analyses that are important for the completeness of our analysis and may be of interest to researchers.
  - Per-protocol analysis - In the per-protocol data analysis, we repeated our primary analysis holding in the intervention arm only subjects who logged onto Thought Spot more than once were considered, as a definition of compliance. As an extension of this analysis, also looked at the moderation effect of compliance.
  - App Usage Analysis – We conducted a descriptive analysis of usage on Thought Spot.
- Blinding: The senior biostatistician analyzing the data was blinded to the treatment group, except for the per-protocol analysis which was conducted last.

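### The exploratory per-protocol analysis sets self-selected repeat users against all controls, so it can show a benefit where none exists; a complier average causal effect with stated assumptions is the better answer

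*Protocol*

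**What the plan says.** The Statistical Analysis Plan section makes intention-to-treat the primary approach: "all participants will be analyzed as they were originally allocated after randomization". The outcome is the formal-source help-seeking score, and the contrast is the between-arm difference in change from baseline to the final time point.

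The Statistical Analysis Plan Change Log then adds, under "We conducted two additional exploratory analyses", a per-protocol repeat of the primary analysis, "holding in the intervention arm only subjects who logged onto Thought Spot more than once were considered, as a definition of compliance". It continues: "As an extension of this analysis, also looked at the moderation effect of compliance". No model is given for that extension. The log mentions no restriction on controls, no adjustment for predictors of use and no caveat about selection, and it does not give the share of repeat users. The senior biostatistician was blinded "except for the per-protocol analysis which was conducted last".

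The Sample size section explains that only the intervention arm had access to the app. On usage data, Adequacy of protection against risks states: "This data will only consist of aggregated (group-level) data about usage trends", and adds that the data are not linked to particular people.

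**The concern.** Logging on a second time happens after randomisation and can be observed in one arm only. Removing intervention participants who did not return, while keeping every control, compares people who chose to engage with an unselected group. The controls include those who would not have engaged had they been given the app. If would-be repeat users would have changed differently anyway, the contrast mixes that difference with any effect of the app.

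The moderation extension has a related problem. Controls have no compliance value, so the data cannot show whether the arm effect differs by compliance. They can show only how users and non-users differ.

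What is at stake is the secondary question of whether the app works when it is used. The same log reports "Since there was no evidence for our primary outcome", so some readers will look to this analysis for that answer.

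**Working it through.** **Inputs from the protocol.** Target effect: d = 0.25, equal to 0.41 points (Sample size; Power Analysis). Implied SD: 0.41 / 0.25 = 1.64 points. Within-subject correlation: 0.6. Attrition: 40%. Per arm: 236 × 0.6 = 141.6, which agrees with the stated 142. The plan gives no figure for the per-protocol analysis, so there is none to reproduce.

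**Inputs not in the documents, so assumed.** c is the share of repeat users. g is the difference in mean change, without the app, between people who would become repeat users and the others. It must be a gap in *change*: a stable difference in level largely cancels in the primary contrast.

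**Bias formula.** Suppose the app does nothing. Let m1 be the mean change in would-be repeat users and m0 that in the others, so g = m1 − m0.

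- Filtered intervention arm: m1
- All controls: c·m1 + (1 − c)·m0
- Difference: (1 − c)·(m1 − m0) = (1 − c)·g

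**Size.** Each cell gives SD units, points (× 1.64) and percentage of the 0.41 target (SD units / 0.25).

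| Repeat users | g = 0.2 SD | g = 0.3 SD | g = 0.5 SD |
|---|---|---|---|
| 30% | 0.14; 0.23; 56% | 0.21; 0.34; 84% | 0.35; 0.57; 140% |
| 50% | 0.10; 0.16; 40% | 0.15; 0.25; 60% | 0.25; 0.41; 100% |
| 80% | 0.04; 0.07; 16% | 0.06; 0.10; 24% | 0.10; 0.16; 40% |

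At g = 0 every cell is zero. A negative g reverses the sign.

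**False-positive rate.** Simulation with 142 per arm, change-score SD 1.64 × √(2 × (1 − 0.6)) = 1.47, a true effect of zero and 6,000 runs per case. Each per-protocol cell gives the bias in points and the two-sided rejection rate at 0.05.

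| g (points) | c = 30% | c = 50% | c = 70% | CACE rejection |
|---|---|---|---|---|
| 0 | 0; 5% | 0; 5% | 0; 5% | 4–5% |
| 0.20 | 0.14; 9% | 0.10; 8% | 0.06; 6% | 4–5% |
| 0.41 | 0.29; 21% | 0.21; 16% | 0.12; 10% | 4–5% |
| 0.82 | 0.57; 64% | 0.41; 50% | 0.25; 26% | 4–5% |

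CACE, the complier average causal effect, is the intention-to-treat difference divided by c. Its mean stayed near zero throughout.

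**If the app does work.** With a true effect of 0.41 in repeat users, none in others, and g = 0.41:

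| | c = 30% | c = 50% | c = 70% |
|---|---|---|---|
| Per-protocol estimate | 0.70 | 0.61 | 0.53 |
| CACE estimate | 0.41 | 0.40 | 0.41 |
| CACE standard error | 0.60 | 0.35 | 0.25 |
| Per-protocol standard error | 0.26 | 0.21 | 0.19 |
| CACE power | 12% | 22% | 38% |
| Intention-to-treat power | about 12% | 21% | 37% |

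**If CACE's exclusion restriction fails.** Suppose people counted as non-users gain 0.10. CACE then estimates 0.41 + 0.10 × (1 − c)/c, which is 0.64, 0.51 and 0.45 at c = 30%, 50% and 70%, against a true 0.41.

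**Moderation.** With no app effect and g = 0.41, the user-minus-non-user contrast within the intervention arm averaged 0.41–0.42. It returns the prognostic gap, not an effect of the app.

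**Usage data.** Adequacy of protection against risks says usage data are group-level only. Against that, Digital data collection draws on individual de-identified accounts. The Digital Data section keeps a list linking identifier, app log-in and name. The Sample size section selects interviewees partly by usage reports, and Other Analyses allows digital data to be correlated with the surveys. The per-protocol rule itself needs each person's log-on count joined to that person's outcome.

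**The case against.** The strongest reply concerns weight. The analysis is labelled exploratory, was run last and supports no confirmatory claim. Its result is not reported in this document, and if it too was null, a bias towards the app would only strengthen that conclusion. This stands, and it limits the point to how the result is presented.

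Several stronger readings are tempting but not supported:

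- **That moderation cannot be estimated at all.** The log says only that the team "also looked at the moderation effect of compliance". Repeat users, other intervention participants and controls can be compared as three groups, or users with non-users inside one arm. Such models can be fitted; they do not identify a causal interaction.
- **That a complier average causal effect is free of bias without conditions.** It needs the exclusion restriction. At the log's cut-off, people who opened the app once count as non-compliers, so a breach is plausible. It also needs an assumption about the expected 40% attrition, and it is affected by the contamination that the Methodology section concedes may occur. Nor does it test moderation, since it sets the effect in non-compliers to zero.
- **That the bias must favour the app, or must be as large as the target.** Both depend on the assumed gap in change, which could be zero or negative. A bias equal to the full target appears only in the upper part of the grid.
- **That the rule was picked because the primary result was null.** The log shows the order of analysis and the unblinding, not when or why the rule was chosen.

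The conflict over usage data is also a separate matter. It does not bear on the validity of the per-protocol contrast, and a complier analysis needs the same individual data.

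**Conclusion.** The point holds for an exploratory analysis. Filtering one arm on behaviour after randomisation breaks the randomised comparison, and the log neither adjusts for this nor warns of it. The bias is (1 − c)·g. It is zero if repeat use is unrelated to prognosis, and 0.04–0.35 SD (16–140% of the 0.41-point target) for assumed shares of 30–80% and assumed gaps in change of 0.2–0.5 SD. The form of the bias is certain; its size and direction in this trial are unknown. The moderation result is a descriptive contrast, not a causal interaction. The primary intention-to-treat conclusion is untouched. The usage-data statements contradict one another and need reconciling in their own right.

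**What to change.** 1. Report a complier average causal effect for the primary outcome, with randomised arm as the instrument, any log-in as the definition of use, the same covariates and a confidence interval. Label it exploratory and post hoc. State its assumptions: exclusion restriction, missing at random under the expected attrition, and no contamination. Present it as the answer to whether the app works if used. The any-log-in definition makes the exclusion restriction more credible, but the estimate then concerns any use rather than repeat use; if nearly everyone logged in, it will lie close to intention-to-treat.
2. Keep the existing per-protocol result only beside an explicit statement that repeat users are self-selected and the comparison is not randomised. Give the repeat-user share.
3. Relabel the moderation result as a within-arm association.
4. Separately, reconcile Adequacy of protection against risks with Sample size, Digital data collection, Digital Data, Other Analyses and the Change Log, so that the document gives one account of whether usage data are individual and linkable.

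Cost: a little analysis work and, for item 4, a wording correction that may need ethics-board notice. The interval will be wider than the per-protocol one, and there is no gain in power over intention-to-treat, so the null conclusion would not be expected to change.
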